### Study oversight and organization

The trial was jointly designed by employees of Boehringer Ingelheim (BI) and the academic investigators who were members of the Steering Committee. The Steering Committee, which was led by the academic investigators and included members who were employees of the sponsor, supervised the trial design and operation. The independent data and safety monitoring committee (DMC) reviews interim safety data every 90 days or on an ad hoc basis on request. A list of committees involved in the trial conduct is presented in Additional file 5.

### Statistical considerations

#### Sample size and power calculations

The primary hypothesis aims to show non-inferiority on 3P-MACE for empagliflozin versus placebo based on a non-inferiority margin of < 1.3 (upper limit of the adjusted 95% confidence interval (CI)) for the hazard ratio. The upper limit of the adjusted 95% CI for the HR of <1.3 was based on FDA guidance for CV trials evaluating new anti-hyperglycemic therapies for T2DM [9]. Patients who receive either 10 mg or 25 mg of empagliflozin will be pooled into a common treatment group for the purposes of the primary analysis. A 4-step hierarchical testing strategy will be followed: 1) non-inferiority test of the primary outcome (3P-MACE), 2) non-inferiority test of the key secondary outcome (4P-MACE), 3) superiority test of the primary outcome (3P-MACE) and 4) superiority test of the key secondary outcome (4P-MACE). A minimum of 691 confirmed primary outcome events are required to provide 90% power with a one-sided α level of 0.025, assuming equal risk between the placebo and empagliflozin groups. With a minimum of 691 events, the trial will also have at least 80% power to detect a hazard ratio of 0.785 (corresponding to a 21.5% risk reduction in CV outcome events) for the primary outcome.

#### Interim analysis

In order to support a CV meta-analysis of all CV events occurring in the phase III trials involving empagliflozin, as required for all New Drug Applications to be submitted to the FDA [9], CV outcome data from the ongoing EMPA-REG OUTCOME™ was extracted. The cut off for the data extraction was preplanned and ~ 150 4P-MACE were included in the project level CV meta-analysis. This resulted in addition of a Haybittle-Peto correction for the interim analysis (i.e., 0.0001 of the α was spent on the data extraction for the interim analysis), and subsequent reduction of the final α level to 0.0249 (in order to maintain the experiment-wise α level of 0.025).

The need to prevent the release of any data from the data extraction or interim analysis that could define the effects of empagliflozin on CV outcomes was fundamental to the study design [23]. Accordingly, procedures, including restricted access to electronic systems, were put in place to ensure that the effect estimate remained blinded and data review by the regulators would not require premature disclosure of the effects of empagliflozin on CV outcome. The data extraction, interim analysis and the following phase III CV meta-analysis were performed by a group independent from the EMPA-REG OUTCOME™ trial team, so that the trial’s operational team and the academic Steering Committee remained blinded to the results. The DMC is the sole group with access to unblinded results beyond the strictly firewalled “CV meta-analysis group” of the sponsor.

#### Analysis plan

Three analysis populations are defined for this trial: 1) The treated set (TS), consisting of all patients who were treated with at least one dose of study drug, 2) The on-treatment set (OS), consisting of patients who received the drug for at least 30 days (cumulative) in whom events will be considered that occurred within 30 days of the off-treatment period or until the end of the entire trial, whichever will be earlier (patients who did not experience the primary outcome will be censored at the end of the treatment period, if the patient completes treatment as planned, or at the end of the 30 day period) and 3) the Full Analysis Set (FAS), consisting of all patients randomized, treated with at least one dose of study drug and with a baseline HbA1c value.

The primary analysis will be based on a Cox proportional hazards model with treatment (with empagliflozin 10 mg and 25 mg pooled into a single group), age, gender, baseline BMI (<30 kg/m^2^, ≥30 kg/m^2^), baseline HbA_1c_ (<8.5%, ≥8.5%), baseline eGFR as well as geographical region (classified as North America, Latin America, Europe, Africa and Asia) as factors. The same Cox proportional hazards model as for the primary outcome will be employed in all steps of the hierarchical testing strategy (3P-MACE and 4P-MACE).

The time to the occurrence of the primary outcome and the key secondary outcomes event will be computed as (event date - randomization date) +1. Patients who do not have the event during the trial period will be censored at the individual day of trial completion. The time to censoring will be computed as (individual day of trial completion – randomization date) + 1. For patients who have more than one primary outcome event during the trial, the time to the first occurrence of the primary outcome event will be considered for the primary analysis. All adjudicated and confirmed events will be used for the primary analysis.

The TS is the basis for the primary analysis and the FAS is the basis for the intention-to-treat (ITT) analysis for efficacy analyses. As sensitivity analyses the primary analysis will also be performed for the OS. Secondary analyses of the primary analysis with pooled active treatment arms will be performed by comparing the active treatments individually versus the placebo arm. Sensitivity analyses of the primary and key secondary outcomes will be performed that include the additional factor of naïve/experienced drug status in the Cox model. The secondary and tertiary further cardiovascular outcomes will be analyzed in a Cox proportional hazards model similar to the primary analysis for the treated set. Of note is that also other sensitivity analysis will be conducted employing other statistical methods, as well as an assessment of outcomes per individual dosages (i.e., empagliflozin 10 mg and empagliflozin 25 mg).

Subgroups to be considered in the analyses will be defined based on, but not limited to, age, HbA1c, BMI, weight, geographical region, race, gender, ethnicity, time since diagnosis of T2DM, renal function, BP, eGFR, glucose-lowering and CV prophylactic medication, CV complications and cohort, all defined at study baseline or screening. In addition, outcomes in patients experiencing severe hypoglycaemia vs those not experiencing severe hypoglycaemia will be assessed. Further details as to the specific categories to be employed for each subgroup factor are provided in Additional file 6.

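### The on-treatment set requires 30 days of drug while time appears to run from randomisation, so the only named on-treatment sensitivity analysis would understate an early harm

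*Protocol article*

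**What the plan says.** All of this stands in the protocol article, under Statistical considerations.

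- **Membership.** The Analysis plan section describes "The on-treatment set (OS), consisting of patients who received the drug for at least 30 days (cumulative". The requirement is met, or not, only after randomisation.
- **Event window.** The same sentence covers patients "in whom events will be considered that occurred within 30 days of the off-treatment period or until the end of the entire trial", whichever comes first. This fixes when the window ends. No start other than randomisation is given.
- **Time origin.** For the primary and key secondary outcomes, time is "computed as (event date - randomization date) +1". No separate origin is given for the on-treatment set (OS).
- **Use of the OS.** "As sensitivity analyses the primary analysis will also be performed for the OS". It is the only named analysis that restricts to on-treatment exposure; further sensitivity analyses by other statistical methods are mentioned without detail.
- **Primary analysis.** "The TS is the basis for the primary analysis", where TS is the treated set: at least one dose, with no minimum exposure.
- **Decision rule.** The Sample size and power calculations section sets a "non-inferiority margin of < 1.3 (upper limit of the adjusted 95% confidence interval (CI)) for the hazard ratio".

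**The concern.** Whether a patient enters the OS can be decided by the outcome itself. A CV death before 30 days of drug makes the criterion impossible to meet. An early MI or stroke after which drug is never resumed has the same effect. In both cases the event leaves the analysis with the patient. Every patient who remains was alive until 30 days of exposure had accrued, yet contributes time from day 1.

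In a non-inferiority trial of CV safety this bears on how the OS result can be used. The primary analysis follows treated patients to trial completion whether or not they are still on drug, and off-drug time can pull a harmful effect toward a hazard ratio of 1. An on-treatment analysis is the usual check on that dilution. If the check is blind to part of any early harm, agreement between it and the primary result reassures less than it appears to.

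**Working it through.** **1. The plan's own figure.** The article states: "A minimum of 691 confirmed primary outcome events are required to provide 90% power with a one-sided α level of 0.025". With the two doses pooled (2:1), the Schoenfeld formula gives

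events = (1.960 + 1.282)² / [(ln 1.3)² × (1/3) × (2/3)] = 687,

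or 688 at the final one-sided 0.0249. This agrees with 691. A 1:1 split gives 611 and does not fit, so 2:1 is the basis used below.

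**2. How many events fall in the first 30 days.** The article gives neither an event rate nor a mean follow-up, so both are assumptions. With a constant hazard and 691 events in 7034 treated patients, rate = 691 / (7034 × F) for mean follow-up F, and early events = 7034 × rate × 30/365.25.

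| Assumed F (years) | Rate per year | Early events | Share of 691 |
|---|---|---|---|
| 2.0 | 4.9% | 28.4 | 4.1% |
| 2.5 | 3.9% | 22.7 | 3.3% |
| 3.0 | 3.3% | 18.9 | 2.7% |
| 3.5 | 2.8% | 16.2 | 2.3% |

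**3. How many of these the rule deletes.** Take 3.4% per year, 40% of events fatal, and 20% of non-fatal events stopping drug for good (all assumed).

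- Early events: 7034 × 0.034 × 30/365.25 = 19.6. An event-time simulation gave about 19.
- Share deleted: 0.40 + 0.60 × 0.20 = 0.52, so about 10 events, or 10/691 = 1.4%.
- Early hazard on active drug tripled: 19.6 × (1/3 + 3 × 2/3) = 45.8 early events, of which 0.52 × 45.8 = 23.8 are deleted. The simulation gave about 45 and 23.

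**4. Effect on the hazard ratio.** Let L = 30/365.25 = 0.0821 years, h the early hazard ratio on active drug (1 thereafter), and f the share of early events deleted. Ignoring discontinuation unrelated to events,

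- all treated: HR = 1 + (h − 1)L/F
- OS: HR = [F − L + h(1 − f)L] / [F − L + (1 − f)L]

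At 3.4% per year, F = 691/(7034 × 0.034) = 2.89 years. With h = 3 and f = 0.52 these give 1.057 and 1.028. The simulation (2:1 allocation, uniform 2.6-year accrual, close at 4.4 years, 8–10% per year discontinuation) compared all treated patients to last dose plus 30 days with the OS as defined, and gave 1.055 and 1.024. Both put the gap at about 0.03.

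Over a wider range, at F = 2.5 years (upper 95% limits in brackets, from SE = 1/√(events × 2/9)):

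| Early HR | All treated | OS, f = 0.3 | OS, f = 0.5 | OS, f = 1.0 |
|---|---|---|---|---|
| 1 | 1.000 (1.171) | 1.000 (1.172) | 1.000 (1.173) | 1.000 (1.174) |
| 2 | 1.033 (1.208) | 1.023 (1.198) | 1.017 (1.191) | 1.000 (1.174) |
| 3 | 1.066 (1.244) | 1.046 (1.224) | 1.033 (1.210) | 1.000 (1.174) |
| 5 | 1.131 (1.317) | 1.093 (1.275) | 1.067 (1.247) | 1.000 (1.174) |

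With no early difference the OS hazard ratio does not move, and non-inferiority power changes only from 90.1% to between 89.2% and 89.9%. Only at an early hazard ratio of 5 do the two analyses fall on opposite sides of 1.3, and that depends on F: at 3.0 years the all-treated upper limit is 1.293.

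**5. Size against sampling error.** ln(1.055/1.024) = 0.030. With 691 events at 2:1 the standard error is 1/√(691 × 2/9) = 0.081, so the shift is 0.37 SE. An on-treatment analysis would have fewer events and a larger SE, making the ratio smaller still. With the same SE the upper limits are about 1.24 and 1.20, both below 1.3.

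**The case against.** A reader might infer that the rule undermines the non-inferiority conclusion, or that the OS is its main safeguard. The document supports neither. The primary analysis is in the treated set, none of the four hierarchical tests is assigned to the OS, and the article calls the OS run a sensitivity analysis without ranking it. In the extreme case tabulated above, the treated-set analysis fails the margin by itself. This part of the objection stands.

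It also stands that the rule is the same in every arm of a double-blind trial, so it distorts the hazard ratio only if early events or early stopping differ by arm. Nor are all early events lost: a patient with an early non-fatal event who goes on to 30 cumulative days of drug keeps that event in the OS. A reader might say that the rule hides more than half of an early signal. That describes a shift of 0.03 on the log scale, under assumed inputs, which the trial could not tell from noise. Early harm can also surface through adjudication of all CV events and deaths, adverse event reporting and the DMC's 90-day reviews.

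Two further arguments carry less weight. First, the randomisation origin for the OS is an inference from the single time formula and from the re-run of the primary analysis, and the full analysis plan may say otherwise. That is a fair caution, but nothing in the article contradicts the inference, and the membership rule itself is explicit. Second, a minimum-exposure set can be a deliberate complement, asking about patients with meaningful exposure. That purpose is legitimate, but it calls for the clock to start once the exposure has been reached.

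**Conclusion.** The point holds as a modest defect in a sensitivity analysis. The OS conditions on a post-randomisation fact that the outcome can determine, and no landmark or delayed entry is described to correct for it. The consequence is limited to how well the OS can corroborate the primary result: it would understate an early harm that the treated-set analysis counts in full.

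Under a constant hazard, 2.3% to 4.1% of the 691 events fall in the first 30 days (assumed mean follow-up 3.5 to 2.0 years). At the assumed rates about 10 are lost. With an assumed tripled early hazard the on-treatment hazard ratio falls from about 1.055 to about 1.024, roughly half of a small excess and under 0.4 SE. The event rate, follow-up, fatal share, stopping share and early hazard ratios are all assumptions. It is worth correcting because the correction is cheap.

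**What to change.** Run the on-treatment sensitivity analysis in all treated patients, from randomisation to 30 days after the last dose or the end of the trial, whichever is earlier, with no minimum exposure.

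If the 30-day minimum is to be kept, let each patient enter the risk set on the day cumulative exposure reaches 30 days (delayed entry), count events from that day only, and tabulate first-30-day events by arm beside the result. In either case, state the time origin for the OS explicitly.

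The cost is a change of wording and one extra model run. No new data are needed, because patients who stop study drug early are already asked to attend all planned visits. The drawback of the first option is that it includes a few patients with very short exposure.

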### Randomization and follow-up

Randomization was undertaken using a computer-generated random sequence and an interactive voice and web response system. Patients were stratified by HbA_1c_ at screening (<8.5%, ≥8.5%), BMI at randomization (<30 kg/m^2^, ≥30 kg/m^2^), region (North America [plus Australia and New Zealand], Latin America, Europe, Africa, Asia), and renal function (eGFR using the Modification of Diet in Renal Disease [MDRD] equation) at screening (Chronic Kidney Disease [CKD] stage 1: ≥90 ml/min/1.73 m^2^; CKD stage 2: 60–89 ml/min/1.73 m^2^; CKD stage 3: 30–59 ml/min/1.73 m^2^). Patients are instructed to attend the clinic at pre-specified times over the duration of the study including a follow-up visit 30 days after the end of the treatment period (Figure 1). Patients who prematurely discontinue study medication are asked to attend all visits as originally planned.

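### In the on-treatment set, events count for 30 days off treatment but event-free completers are censored at the end of treatment: a minor mismatch in a sensitivity analysis

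*Protocol article*

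**What the plan says.** The Analysis plan section admits patients with at least 30 days of cumulative exposure to the on-treatment set (OS) and gives all of them one event window: "events will be considered that occurred within 30 days of the off-treatment period or until the end of the entire trial, whichever will be earlier". A bracket then gives event-free patients two censoring dates. For the first group, "patients who did not experience the primary outcome will be censored at the end of the treatment period, if the patient completes treatment as planned"; the rest are censored "or at the end of the 30 day period".

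The Randomization and follow-up section has patients attend visits "over the duration of the study including a follow-up visit 30 days after the end of the treatment period".

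The OS has a limited role: "As sensitivity analyses the primary analysis will also be performed for the OS". The main result comes from another set ("The TS is the basis for the primary analysis"), which has its own rule: "Patients who do not have the event during the trial period will be censored at the individual day of trial completion".

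**The concern.** For a patient who stops early, events and censoring both run to 30 days off treatment. For a patient who completes as planned, events run to 30 days off treatment but event-free follow-up stops at the end of treatment. Take two completers with the same length of treatment, one of whom has an infarction on day 15 after the last dose. That event is counted at its own date. The other completer, also followed on day 15 and event-free, left the risk set 15 days earlier.

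Whether a completer is followed past treatment thus depends on the outcome. A time-to-event analysis assumes that censoring does not depend on the outcome in this way. At stake are absolute on-treatment rates, which would be too high in every arm, and the clarity of the one exposure-based check on the primary result that the article names.

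**Working it through.** **1. Does the trial-end cap close the gap?** The rules side by side:

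| Patient | Events count to | Event-free patient censored at |
|---|---|---|
| Stops early | 30 days off treatment, or trial end if sooner | end of the 30 days |
| Completes as planned | 30 days off treatment, or trial end if sooner | end of treatment |

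The completer row would be consistent only if the trial ended, for that patient, on the last day of treatment. The follow-up visit 30 days later lies within the study, so the cap does not remove the mismatch.

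**2. The plan's own figure.** This point disputes no stated number. For context, the 691 events follow from the Schoenfeld formula with margin 1.3, 90% power, one-sided 0.025 and one third of patients on placebo:

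events = (1.960 + 1.282)² / [(1/3)(2/3)(ln 1.3)²] = 10.51 / (0.2222 × 0.06884) ≈ 687

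At 0.0249 the result is 688. Both agree with the stated minimum.

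**3. Events counted and time dropped.** From the article: 7034 treated patients (slightly more than the OS, which requires 30 days of exposure) and a 30-day window. Assumed, because the article gives neither: an event rate of 2–4% per year, and 70–90% of patients reaching the planned end of treatment event-free. With at least 691 events, no more than 1 − 691/7034 = 90% can be event-free.

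- Dropped time = 7034 × share × 30/365. Share 0.7 gives 405 patient-years; share 0.9 gives 520.
- Counted events = dropped time × rate. 405 × 0.02 = 8.1; 520 × 0.04 = 20.8.
- Against 691 events, that is 8.1/691 = 1.2% to 20.8/691 = 3.0%.

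**4. Effect on the event rate.** Simulation of 7034 patients allocated 2:1, 150 runs per scenario. Assumed: 3.5% per year on placebo, 7% per year discontinuation, uniform entry over 2.6 years (the stated recruitment period) and a common end of treatment at 4.6 years. The 30-day exposure requirement was not imposed. With equal risks, 699 events were counted, 14.4 of them in completers after treatment, and 409 patient-years were dropped. The rate was 0.03568 as written and 0.03495 with 30 days for both events and censoring: 0.03568/0.03495 = 1.021, or about 2% too high.

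**5. Effect on the pooled hazard ratio.** Same simulation, Cox model with treatment only:

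| True HR on / after treatment | As written | 30 days for both | Completers: end of treatment for both |
|---|---|---|---|
| 1 / 1 | 1.0127 | 1.0127 | 1.0133 |
| 0.785 / 0.785 | 0.7911 | 0.7911 | 0.7912 |
| 0.785 / 1 | 0.7962 | 0.7963 | 0.7911 |
| 0.785 / 1.3 | 0.7974 | 0.7976 | 0.7852 |
| 1.3 / 1.3 | 1.2870 | 1.2872 | 1.2836 |
| 1.3 / 1 | 1.3012 | 1.3012 | 1.3089 |

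The rule as written differs from the matched 30-day rule by at most 0.0002. The reason is that event-free completers leave both arms in similar proportion, so the make-up of each late risk set hardly changes. The larger gaps to the last column, up to 0.7974 − 0.7852 = 0.0122, arise because that rule leaves out completers' off-drug events. They do not come from the mismatch.

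**6. Effect on cumulative incidence.** A similar simulation (common end at 4.5 years, 8% per year discontinuation, 300 runs) gave these differences, as written minus the matched rule:

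| Years | Difference (points) | At risk |
|---|---|---|
| 3 | +0.14 | about 2,900 |
| 3.5 | +0.24 | not recorded |
| 4 | +0.40 | about 860 |
| 4.4 | +0.80 | not recorded |
| 4.49 | +1.34 | about 17 |

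**The case against.** The strongest defence is that the sentence is compressed rather than wrong. Its event clause and its bracket each have two limbs, which may have been meant to correspond, with trial end standing for end of treatment in completers. The article does not define trial end or individual trial completion relative to the last dose, and the full protocol is not shown. But the words do not make that link, the 30-day visit points the other way, and a programmer following the text would count the events and drop the time. Even on the kinder reading a clarifying clause is needed.

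The second defence is that nothing planned is harmed. The article assigns the OS only a repeat of the Cox analysis, no step of the hierarchical tests uses it, and the article names no on-treatment rate or Kaplan-Meier curve for it. This largely stands, and it limits the weight of the point.

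A reader might infer more than the article supports:

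- **That the non-inferiority or superiority result is biased.** The treated-set rule is separate, and the OS hazard ratio hardly moves.
- **That post-treatment events enter with no time at risk.** Patients with events contribute their own time up to the event. The missing time is that of event-free completers.
- **That the on-treatment curve is wrong by more than a percentage point.** In the simulation this appears only within days of the assumed common stop, with about 17 of 7034 patients at risk.

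**Conclusion.** The rule as stated is inconsistent for patients who complete treatment, because their follow-up after treatment depends on having an event. The counts of about 8–21 events and about 400–520 patient-years rest on assumed event and completion rates. The 2% inflation of the crude rate and the incidence differences (0.14–0.40 points from 3 to 4 years) also rest on assumed discontinuation, uniform entry and a common end of treatment. The finding that the hazard ratio is essentially unchanged rests on discontinuation being similar across arms in the runs shown. This is a minor error in a sensitivity set. It should be corrected because it is plain in the text and cheap to fix, not because it threatens a conclusion of the trial.

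**What to change.** Use one cut-off per patient in the OS definition, applied to both events and censoring. The preferred form censors event-free completers at the earlier of 30 days after the last dose and individual trial completion, which treats them like early stoppers. It takes one clause and no new data, since the 30-day visit is already scheduled and cardiovascular events are already adjudicated.

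It has a small downside: some off-drug time stays in a set called on-treatment, which can dilute an on-drug effect. With a true hazard ratio of 0.785 on treatment and none after, the estimate is 0.796 instead of 0.791. The text as written already counts those off-drug events, so this adds no dilution to the current rule. The alternative is to end both events and censoring at the end of treatment for completers, which is closer to a strict on-drug estimate but gives up about 8–21 events under the assumptions above. Either is coherent. The choice should be stated before unblinding, together with what trial end means for a completer.
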